### Procedure

Approval for the study has been obtained from five hospital ethics committees (Kowloon West Cluster Research Committee; Hong Kong East Cluster Ethics Committee; Kowloon Central/Kowloon East Research Ethics Committee; Hong Kong West Cluster Ethics Committee; and New Territories West Cluster Clinical & Research Ethics Committee). To ensure the rights of all participants will be protected, the research carried out will be in compliance with the Helsinki Declaration (http://www.wma.net/en/30publications/10policies/b3/index.html). Research assistants will approach patients in the oncology out-patient clinic and ask them whether they are smokers or not. The eligible subjects will then invite to participate in this study after they are told the purpose of the study. They will be given the option of participating or refusing involvement in the study and will be told that their participation is voluntary without prejudice. Written consent will then obtain from all participants.

To evaluate the effectiveness of a smoking cessation intervention using risk communication approach, a total of 560 eligible Chinese cancer patients were recruited from five out-patient clinics in Hong Kong. After completing the baseline questionnaire, subjects will receive proposed intervention according to their group assignment. Four consecutive (3-, 6-, 9- and 12-month) follow ups will be conducted by trained interviewers (blinded to the group assignment) with all subjects via telephone. We will assess hospital readmission and other clinical outcomes from the participants’ medical records accordingly. Patients who have successfully quit smoking at 6-month will be invited to come back to the out-patient clinic and have biochemical validation tests (saliva cotinine test and exhaled CO test). We will offer HKD300 (USD38.5) per client to cover their travel expenses and time cost. From our previous experience, such an incentive is necessary to secure a sufficiently high response rate.

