### Primary and secondary outcomes

The primary outcome is the self-reported 7-day point prevalence (PP) quit rate of the smoking cancer patients during 6-month follow up. The secondary outcomes include (a) self-reported 7-day PP quit rate at 12-month follow-up and the biochemically validated quit rate at 6-month follow-up (non-smoking status is confirmed by a carbon monoxide level in expired air < 9 ppm and saliva cotinine level < 115 ng/mL in parallel test), (b) percentage of patients reduced smoking by at least 50 % at 6- and 12-month follow-up compared to baseline, (c) percentage of patients with quit attempt(s) at 6- and 12-month follow-up, (d) change in the intention to quit smoking (stage of readiness to quit) at 6- and 12-month follow-up compared to baseline, (e) change in risk perceptions of continued smoking at 6- and 12-month follow-up compared to baseline, and (f) change in health-related quality of life at 6- and 12-month compared to baseline.

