### Analysis

Data analysis was performed using the Statistical Package for Social Science software, version 20.0 for Windows. When assessing the effectiveness of interventions between the two groups, we will first compare the baseline characteristics of the patients using chi-square test for categorical variables and *t*-test or Wilcoxon rank-sum test for continuous variables between the experimental and control groups. The primary analysis will be an unadjusted intention-to-treat analysis of the difference in self-reported 7-day point prevalence quit rate of the smoking cancer patients during 6-month follow up between the two groups. The analysis will be performed using Pearson’s chi-square test or with the use of Fisher’s exact test, if there were five or fewer participants per cell. Similar approach will be used to estimate the differences in secondary outcomes (e.g. self-reported 7-day PP quit rate at 12-month follow-up and the biochemically validated quit rate at 6-month follow-up, percentage of patients reduced smoking by at least 50 % at 6- and 12-month follow-up compared to baseline, and quality of life at 6 and 12 months) between groups. Crude odds ratios (ORs) for quitting will be estimated using logistic regression model and were compared with ORs that were adjusted for baseline variables (e.g. sex, age, education, stage of readiness). Those who are lost to follow-up or refuse to participate in the validation tests, will be treated as smokers with no reduction in cigarette consumption compared with (a) baseline, as the main analysis (by intention to treat), (b) the most recent level and (c) complete case (per protocol) analysis by excluding subjects with missing data as a sensitivity analysis.

For the process evaluation, all qualitative data from interviews will be tape-recorded and transcribed verbatim. Content analysis will be employed and themes identified. The constant comparative method will be used to search for common constructs and themes about the implementation and the effect of the intervention as perceived by the participating subjects.

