### Potential limitations or barriers

There are serval potential limitations or barriers of implementing the proposed intervention in clinical practice. First, the proposed intervention is relatively comprehensive, which generally takes 30 to 45 min to implement including the baseline assessment. According to our previous smoking cessation projects in outpatient clinics, some patients are too impatient to undergo a long intervention and some are reluctant to participate for fear that they might miss or experience delays in their medical consultation or other medical procedures. Nevertheless, the intervention will only implement during the waiting time for medical consultation in the out-patient clinics and all potential subjects will be reinforced by nurse counsellors that they will not miss the medical consultation or medical procedures through participating in this study. Second, the intervention that we proposed for the experimental group is not on a one-off basis. Each subject will receive at least one boost up telephone intervention within one week and another telephone intervention within one month by a nurse counsellor. Such practice may not be feasible in busy clinical settings in Hong Kong at this moment. Nevertheless, such approach is necessary and crucial as smoking is addictive and quitting is very difficult, with a high rate of relapse. Based on our previous smoking cessation projects on promoting smoking cessation, continuous reminding and offering support is of paramount importance to achieve the ultimate goal of complete cessation. Indeed, each telephone counselling will take only 10–15 min. If the telephone follow up effect size is proven and substantial, this would justify additional resources for such practice. In the short run, smokers may be referred to smoking cessation hotline for continuous support and follow up after receiving the initial intervention by healthcare professionals. Third, we do not use biochemical indicator as the primary outcome, which is more scientific and objective to ascertain whether a person has successfully quitted smoking. Nevertheless, using biochemical validation is costly, difficult to obtain for all subjects, and may not correspond to the time frame of the assessment. Furthermore, the response rate for participating in biochemical validation is far less than self-report; this situation is not only in Hong Kong but also has been reported in elsewhere [29]. In fact, subjects might refuse to comply with a biochemical validation for a wide variety of reasons unrelated to smoking status, continuing to classify all these subjects as smokers would represent a distortion of the outcome data, resulting in a gross overestimate of smoking rates. After that, we decide to use self-reported 7-day point prevalence quit rate as the primary outcome.

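### As worded, the rule that counts validation refusers as smokers is not limited to the validated quit rate, and so conflicts with the self-reported primary outcome

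*Protocol article*

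**What the plan says.** Four places in the protocol article bear on this.

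- **Primary and secondary outcomes.** This section defines the main endpoint by self-report alone: "The primary outcome is the self-reported 7-day point prevalence (PP) quit rate of the smoking cancer patients during 6-month follow up". Validated quitting is listed separately, among the secondary endpoints: "the biochemically validated quit rate at 6-month follow-up (non-smoking status is confirmed by a carbon monoxide level in expired air".
- **Procedure.** Validation is offered to one subgroup only: "Patients who have successfully quit smoking at 6-month will be invited to come back to the out-patient clinic and have biochemical validation tests".
- **Analysis.** "The primary analysis will be an unadjusted intention-to-treat analysis of the difference in self-reported 7-day point prevalence quit rate". The closing sentence of the same paragraph gives the handling rule: "Those who are lost to follow-up or refuse to participate in the validation tests, will be treated as smokers with no reduction". Reduction here refers to cigarettes smoked relative to baseline, and this coding is labelled "as the main analysis (by intention to treat". Carrying forward the most recent level and a complete-case analysis follow as alternatives.
- **Potential limitations or barriers.** Here the authors defend a self-reported primary outcome. They say patients decline validation for many reasons unconnected with whether they smoke, and that "continuing to classify all these subjects as smokers would represent a distortion of the outcome data".

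**The concern.** The handling rule joins two different situations with one conjunction. A patient lost to follow-up has no 6-month self-report. A patient who declines the validation visit does have one, and it says that the patient has quit. Nothing is missing for that patient on the primary outcome.

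The rule treats both alike, carries the intention-to-treat label that the primary analysis also carries, and names no outcome to which it is confined. An analyst who follows it to the letter would score the primary outcome as reported quitting plus willingness to return for a test. That is not the outcome defined, nor the one on which the sample size rests. It is not validated abstinence either: the stated rule recodes a quitter who declines the test but says nothing that would recode one who takes it and fails. The reduction outcome (at least 50 % fewer cigarettes) would be altered in the same way, although no validation step is described for it.

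At stake are the level of both quit rates, the power of the primary comparison and, if refusal differs by arm, the estimated effect. Unresolved wording also leaves two possible primary results to choose from once data are in.

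**Working it through.** **Step 1: who can be affected.** Only 6-month quitters are invited to validation (Procedure). Refusal can therefore change a patient's primary outcome in one direction only, from quit to smoking.

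**Step 2: reproduce the planning figure.** Inputs from Power calculation: 29 % and 18 % self-reported quitting, 5 % significance (taken as two-sided), power 0.80. With the pooled normal approximation and mean rate 0.235:

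n = [1.96·√(2·0.235·0.765) + 0.8416·√(0.29·0.71 + 0.18·0.82)]² / 0.11² = (1.1753 + 0.5004)² / 0.0121 = 232.05, rounded up to 233.

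This matches the stated 233. Then 233/0.85 = 274, also as stated. With 274/20 = 13.7 patients per cluster and an intra-class correlation of 0.002, 274 × (1 + 12.7 × 0.002) = 281, against the stated 280. The design thus rests on purely self-reported rates.

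**Step 3: apply the rule literally.** Let r be the share of self-reported quitters who refuse validation. The article gives no value, saying only that participation is well below that for self-report, so r is assumed. With 15 % lost and coded as smokers, the analysed rates are

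- intervention: 0.29 × 0.85 × (1 − r)
- control: 0.18 × 0.85 × (1 − r)

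Power at n = 280 per arm, with p̄ the mean of the two rates, is Φ{[(p₁ − p₂)√n − 1.96√(2p̄(1 − p̄))] / √(p₁(1 − p₁) + p₂(1 − p₂))}. For r = 0: (0.0935 × 16.733 − 1.1082) / 0.5615 = 0.813, giving power 0.79.

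| Refusal r (assumed, equal in both arms) | Intervention | Control | Difference (points) | Power, 15 % lost coded as smoking | Power, no loss |
|---|---|---|---|---|---|
| 0 % | 24.7 % | 15.3 % | 9.4 | 0.79 | 0.87 |
| 20 % | 19.7 % | 12.2 % | 7.5 | 0.68 | 0.76 |
| 30 % | 17.3 % | 10.7 % | 6.5 | 0.61 | 0.69 |
| 50 % | 12.3 % | 7.7 % | 4.7 | 0.45 | 0.52 |

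Rates and differences are for the case with 15 % lost; differences come from unrounded rates. Clustering is ignored. The plan's own allowance for it is small (274 to 280, about 2 %).

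The 0 % row is the comparator. The step from 0.87 to 0.79 comes from coding losses as smoking and is not part of this point. Only the fall below 0.79 is due to the refusal clause.

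**Step 4: unequal refusal.** With 15 % lost coded as smoking, against the 9.4-point reference:

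- 40 % refusal in the intervention arm, 20 % in control: 0.29 × 0.85 × 0.6 = 14.8 % against 0.18 × 0.85 × 0.8 = 12.2 %, a difference of 2.6 points.
- 20 % in the intervention arm, 40 % in control: 19.7 % against 9.2 %, a difference of 10.5 points.

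These show only that bias can go either way. Nothing in the article indicates which direction, if either, to expect.

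**The case against.** The best defence is that the sentence is a missing-data rule for a paragraph covering several outcomes. Loss to follow-up leaves the self-report missing, and refusal leaves the validation result missing. The complete-case alternative excludes subjects with missing data, and a refuser's self-report is not missing. The article calls the primary outcome self-reported throughout, and the limitations section suggests the authors would not want refusers to drive it. On that reading refusal matters only for the validated secondary rate and there is no conflict. The article is also a condensation, and a fuller document might assign each rule to its outcome.

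Much of this stands as evidence of intent. A reader might infer that the authors decided to replace the self-reported primary outcome with a partly validated one; the documents do not support that. They support only that the sentence, taken as written, has that effect.

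It does not remove the conflict. No words confine the refusal clause to the validated rate, and the clause also fixes cigarette consumption, an outcome with no validation step. A stated rule that contradicts the stated rationale is different from a detail left to another document.

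The objection also limits the size of the claim. Refusal rates are unknown, and the travel payment (HKD300) is there to keep uptake high. A reader might infer that closer nurse contact makes the intervention arm more willing to return and so biases the result in its favour. The article does not establish this: controls also receive brief face-to-face counselling and nurse telephone contact. Finally, self-reports are collected by telephone regardless of validation, so the outcome as defined can always be computed.

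**Conclusion.** The point holds as a conflict in wording. The literal rule recodes observed successes on the primary outcome, and the article elsewhere rejects that coding. Whether the authors intended it is uncertain, and the narrower intention is plausible.

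If the rule were applied literally, power under equal refusal of 20 % to 50 % would fall from 0.79 to between 0.68 and 0.45. This rests on the planning rates of 29 % and 18 %, 280 per arm, 15 % attrition coded as smoking, assumed refusal rates and no allowance for clustering. Under unequal refusal the difference itself would be biased, in a direction the documents do not determine. The conflict does not depend on these figures. Because the wording decides who counts as a success on the primary outcome, it should be settled before the analysis.

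**What to change.** Replace the single rule with one for each type of outcome:

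1. For self-reported 7-day abstinence and for reduction of at least 50 %, count as smokers with no reduction only those patients who have no self-report at the visit in question. Declining validation never changes an observed self-report.
2. For the biochemically validated quit rate only, count refusers and non-attenders as not validated.
3. Report validation uptake among self-reported quitters by arm.

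The cost is a sentence or two in the Analysis section and one extra line in the results. Design, conduct and data collection are unaffected. If the refusal clause was always meant for the validated rate alone, the change simply records that.

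### For the biochemically validated 6-month quit rate, excluding test refusers under sensitivity rule (c) removes only claimed quitters, so it is not a neutral complete-case check

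*Protocol article*

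**What the plan says.** The Primary and secondary outcomes section lists "the biochemically validated quit rate at 6-month follow-up" as a secondary outcome, defined by exhaled carbon monoxide and saliva cotinine together. The Procedure section says who is tested: "Patients who have successfully quit smoking at 6-month will be invited to come back to the out-patient clinic and have biochemical validation tests".

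The Analysis section names two ways in which data can be missing and gives both one main rule: "Those who are lost to follow-up or refuse to participate in the validation tests, will be treated as smokers". The sensitivity rule that goes with it is "c) complete case (per protocol) analysis by excluding subjects with missing data as a sensitivity analysis". The same section includes the validated quit rate among the outcomes to be compared between groups, and does not define missing data separately for it.

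Under Potential limitations or barriers the article expects that "the response rate for participating in biochemical validation is far less than self-report" and that "subjects might refuse to comply with a biochemical validation for a wide variety of reasons unrelated to smoking status". It concludes that "continuing to classify all these subjects as smokers would represent a distortion of the outcome data, resulting in a gross overestimate of smoking rates".

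**The concern.** A complete-case analysis is a useful check on counting missing as smoking when the people dropped could have had either result. That holds for loss to telephone follow-up. It does not hold for refusal of the test: a patient who reports smoking is never invited and so cannot refuse. Excluding refusers therefore selects on the reported outcome.

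The article regards counting refusers as smokers as a distortion. On its own view of why people refuse, rule (c) removes only part of that distortion. The validated rate is the objective support for a self-reported primary outcome, so readers will look to this sensitivity analysis to judge whether low test uptake matters.

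**Working it through.** **Inputs from the article.** Self-reported quit rates at 6 months are 29 % and 18 %, and attrition is 15 % (Power calculation). There are 280 patients per arm, with 81 quitters expected in the experimental arm (Implications for clinical practice); 280 × 0.29 = 81.2 reproduces that figure. The article gives no validated rate, refusal rate or pass rate.

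**Assumptions.** A share c = 0.9 of claimed quitters would pass, the same in refusers as in those tested. A share f = 0.5 refuse in both arms, with a range of 0.3 to 0.7. Attrition is set aside at first.

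**Formulas**, with s the self-reported quit rate:
- everyone tested: s × c
- main rule (refuser counted as smoker): s(1 − f)c
- rule (c), refusers excluded: s(1 − f)c / (1 − s f)

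**Equal refusal, f = 0.5**

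| Analysis | Experimental | Control | Difference | Odds ratio |
|---|---|---|---|---|
| Everyone tested | 0.29 × 0.9 = 26.1 % | 0.18 × 0.9 = 16.2 % | 9.9 points | 1.83 |
| Main rule | 0.1305 = 13.1 % | 0.081 = 8.1 % | 4.95 points | 1.70 |
| Rule (c) | 0.1305/0.855 = 15.3 % | 0.081/0.910 = 8.9 % | 6.4 points | 1.84 |

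The rule (c) difference is 1 − 6.36/9.9 = 36 % too small. At f = 0.3 it is 19 % too small and at f = 0.7 it is 57 % too small. These percentages do not depend on c, which cancels.

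**Unequal refusal** (odds ratio with everyone tested: 1.83)

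| Refusal, experimental / control | Main rule | Rule (c) |
|---|---|---|
| 60 % / 40 % | 1.08 | 1.24 |
| 40 % / 60 % | 2.68 | 2.75 |

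**With attrition.** Take 280 per arm and 42 lost (15 %), which leaves 238 followed. Assume that half of the claimed quitters attend and that 80 % of those tested pass.
- Experimental: 81 claimed quitters, 41 tested, 40 refuse, 0.8 × 41 = 32.8 validated. Main rule 32.8/280 = 11.7 %. Rule (c) 32.8/(280 − 42 − 40) = 16.6 %. If refusers also pass at 80 %: (32.8 + 32)/238 = 27.2 %.
- Control: 50 claimed quitters, 25 tested, 25 refuse, 20 validated. Rule (c) 20/213 = 9.4 %. If refusers pass at 80 %: 40/238 = 16.8 %.

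The difference shrinks from 10.4 to 7.2 points, the same pattern.

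**Direction.** Let p be the share of refusers who would pass, V the validated, R the refusers and F the followed. Rule (c) gives V/(F − R) and full testing gives (V + pR)/F. Rule (c) is the lower of the two only if p > V/(F − R). In the experimental-arm example the break-even is p = 16.6 %; at p = 0 full testing gives 32.8/238 = 13.8 %, and rule (c) overstates. For the risk difference in the no-attrition example, full testing gives 4.95 + 5.5p points (0.29 × 0.5 − 0.18 × 0.5 = 0.055). This equals rule (c)'s 6.36 points at p = 1.41/5.5, or about 26 %.

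**The case against.** The strongest reply compares rule (c) with the main rule it is meant to check. Under equal refusal it moves the right way: 6.4 points against 4.95, where full testing gives 9.9. It also nearly restores the odds ratio (1.84 against 1.83, with 1.70 under the main rule), and the Analysis section names the odds ratio as an effect measure for quitting. Unequal refusal harms the main rule just as much. All of this stands. It means that rule (c) is an incomplete correction and not a step in the wrong direction, and that differential refusal is not a weakness of rule (c) alone.

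It also stands that the size rests on assumed refusal and pass rates, and that the authors recognise low uptake and for that reason made self-report primary.

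The reply that such detail belongs in the full protocol or analysis plan is weaker. The article does not leave the rule open: it names test refusal as missing data and says that such subjects are excluded.

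Two stronger readings are tempting and are not supported. A reader might infer that excluding refusers deletes only true successes. Refusers are claimed quitters of unknown status, and some could fail the test. A reader might also infer that everyone without a test result is excluded, self-reported smokers included, so that only the pass rate among those tested remains and the arms cannot differ. The Analysis section describes the missing as those lost or refusing. A self-reported smoker who was never invited is neither, and is known not to be a validated quitter.

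**Conclusion.** The point holds in a limited form. For the validated quit rate, rule (c) selects on the reported outcome and is not a neutral complete-case check. On the article's own premise that refusal is largely unrelated to smoking, it understates the rate in each arm and the risk difference: by 36 % at an assumed 50 % refusal, and by 19 % to 57 % over 30 % to 70 % refusal, with equal refusal and equal pass rates in refusers and those tested.

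Understatement is conditional. It reverses for the rate if fewer than about 17 % of refusers would pass (experimental-arm example with attrition), and for the risk difference below about 26 % (example without attrition). The odds ratio is nearly unaffected under equal refusal and is distorted when refusal differs by arm, as it is under the main rule.

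The rule can be computed and is an ordinary complete-case analysis for the primary self-reported outcome, which does not use the test. Severity is minor: one sensitivity analysis of one secondary outcome.

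**What to change.** In the Analysis section, apply rule (c) only to loss of the telephone follow-up. For the validated quit rate, keep self-reported smokers as smokers and show three results for claimed quitters who refuse the test:

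1. None pass (the existing main rule).
2. They pass at the rate of tested quitters in the same arm, computed as self-reported quit rate × proportion confirmed, or by multiple imputation.
3. All pass.

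With the equal-refusal inputs above, the differences would be 4.95, 9.9 and 10.45 points; for the last, (0.1305 + 0.145) − (0.081 + 0.09) = 0.1045.

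Report test uptake by arm beside these results. Under unequal refusal the none-pass version is not conservative for the treatment effect (odds ratio 2.68 against 1.83 when controls refuse more).

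The cost is a change of wording and a short computation on data already collected, with no new patients or tests. The drawback is that the middle result assumes refusers resemble tested quitters of the same arm. The data cannot verify this, so that result must be shown beside the other two.
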